## Abstract

**Background:**

Symptom checker apps (SCAs) are accessible tools that provide early symptom assessment for users. The ethical, legal, and social implications of SCAs and their impact on the patient-physician relationship, the health care providers, and the health care system have sparsely been examined. This study protocol describes an approach to investigate the possible impacts and implications of SCAs on different levels of health care provision. It considers the perspectives of the users, nonusers, general practitioners (GPs), and health care experts.

**Objective:**

We aim to assess a comprehensive overview of the use of SCAs and address problematic issues, if any. The primary outcomes of this study are empirically informed multi-perspective recommendations for different stakeholders on the ethical, legal, and social implications of SCAs.

**Methods:**

Quantitative and qualitative methods will be used in several overlapping and interconnected study phases. In study phase 1, a comprehensive literature review will be conducted to assess the ethical, legal, social, and systemic impacts of SCAs. Study phase 2 comprises a survey that will be analyzed with a logistic regression. It aims to assess the user degree of SCAs in Germany as well as the predictors for SCA usage. Study phase 3 will investigate self-observational diaries and user interviews, which will be analyzed as integrated cases to assess user perspectives, usage pattern, and arising problems. Study phase 4 will comprise GP interviews to assess their experiences, perspectives, self-image, and concepts and will be analyzed with the basic procedure by Kruse. Moreover, interviews with health care experts will be conducted in study phase 3 and will be analyzed by using the reflexive thematical analysis approach of Braun and Clark.

**Results:**

Study phase 1 will be completed in November 2021. We expect the results of study phase 2 in December 2021 and February 2022. In study phase 3, interviews are currently being conducted. The final study endpoint will be in February 2023.

**Conclusions:**

The possible ethical, legal, social, and systemic impacts of a widespread use of SCAs that affect stakeholders and stakeholder groups on different levels of health care will be identified. The proposed methodological approach provides a multifaceted and diverse empirical basis for a broad discussion on these implications.

**Trial Registration:**

German Clinical Trials Register (DRKS) DRKS00022465; https://tinyurl.com/yx53er67

**International Registered Report Identifier (IRRID):**

DERR1-10.2196/34026

## Introduction

### Background

The number of health-related software in consumer and research-oriented apps is increasing rapidly. Symptom Checker Apps (SCAs) are one example for health-related software that could have a major impact on health systems on all levels. SCAs process medical symptoms that users enter by applying algorithms and databases with medical information [1]. Based on these symptoms, SCAs generate a list of probable causes and suggest medical follow-up actions (eg, wait at home, see a doctor, go to the emergency room). The Google Play Store already lists 249 apps (retrieved on March 24, 2021) for the key words “symptom checker” [2]. Some SCA manufacturers advertise that they have implemented artificial intelligence [1,3,4] and big data as the basis of their apps. For example, as described by Richens et al [5], the SCA “Babylon” uses a causal machine learning approach based on a Bayesian approach combined with counterfactual inference. The presented algorithm achieved expert clinical accuracy for a test set of clinical vignettes [1]. It, however, remains unclear how well it performs in real-life situations. Although there have already been strong claims from ethical research that emphasize the significance of criteria such as transparency, trustworthiness, agency, and responsibility for artificial intelligence–driven decision support systems such as SCAs [6-8], not all manufacturers using artificial intelligence consider these criteria, and it is mainly untransparent how user data are processed and algorithms are trained.

The regulation of SCAs varies in different countries. In some countries, SCAs are effectively unregulated (eg, Australia [9]); in others, SCAs are regulated but with a period of “enforcement discretion” without active regulatory (eg, US Food and Drug Administration [10]). In the European Union, there is a transition between regulation through manufacturer “Declaration” of conformity to legislation toward a model of regulator audit of compliance with standards, including the formal reporting and evaluation of specified forms of clinical data and surveillance trends [11].

Symptom checkers are low-threshold tools that can be accessed with a suitable electronic device with internet access such as a smartphone and are available as apps or as browser versions. Users must be able to interact with technical devices and to interpret the SCA’s output to utilize them properly. This could lead to a disadvantage of specific population groups, for example, older adults, people with disabilities [12], or people with limited economic resources [13]. Some SCAs exclude specific user groups for symptom analysis, for example, pregnant women, children, older adults, and patients with specific comorbidities [14].

A recent study by Aboueid et al [15] investigated the intention to use symptom checkers for self-triage and revealed 5 profiles by using a latent class analysis: tech acceptors, tech rejectors, skeptics, unsure acceptors, and tech seekers. Tech seekers, which were described as participants who have positive perspectives related to SCA functionality and artificial intelligence but do not perceive to have access to the technology, showed the highest odds to use SCAs. However, the sample investigated only students aged between 18 and 34 years [15].

Although some users found that SCAs are useful tools for self-diagnosis and even reported positive health effects [16], other users had problems providing and interpreting concrete information on symptom time patterns or severity [17].

SCAs recommend actions and probable causes for the entered symptoms through their output if the output is incongruent with the users’ experience or if expectation discrepancies arise [18] and may initiate unnecessary health care–seeking behavior [19].

In terms of their medical value and validity, commercially available SCAs still have problems with accurate triage (determining a user’s medical condition based on their input and recommending the optimal health-related actions for the user). Several studies showed that SCAs often suggested risk-averse action recommendations [20-22]. SCA diagnostic and triage accuracy is still limited and was even less reliable in nonurgent scenarios, which are common in primary care [20,23]. A recently published study compared the performance of SCAs (n=8) with the performance of telephone consultation with the general practitioner (GP) (n=7) by using case vignettes (n=100). GPs outperformed SCAs on all assessed outcomes (accuracy, condition suggestion, appropriateness, and safety of urgency advice). The comparison was limited to telephone consultations and did not comprise direct patient-physician contact. Another recent study compared the performance of SCAs to that of medical laypersons using clinical vignettes and found that most laypersons outperformed the majority of SCAs, even though SCAs detected emergency cases more reliably than the laypersons [23].

In high-performing health care systems, inaccurate triage can cause preventable costs and increase the risk of unnecessary procedures that could lead to avoidable risks for patient’s safety [3,24]. However, in structurally weak regions with restricted access to medical care, SCAs can provide a first-line assessment that otherwise would not be available [25].

In summary, the potential risks of the use of SCAs (exclusion of users, stress, and induction of health-seeking behavior) contrast the advertised opportunities of SCAs such as patient empowerment and better health care for underserved regions. There is a substantial gap in the literature concerning the effect of SCAs on different health care systems, different levels of health care (microlevel, mesolevel, and macrolevel [26]) within these systems, and the system’s different participants (users, nonusers, and health care providers). If SCAs become more widely used, their ethical, legal, social, and systemic impacts on these levels and participants must be better understood despite complex interactions and methodological challenges. In this study, we aim to clarify the ethical, legal, social, and systemic impacts of SCAs on users, nonusers, GPs, the primary health care systems, and their work by means of an independent, empirical, integrated multi-perspective, and multidisciplinary discussion.

### Objectives

Owing to the lack of systematic research of SCAs in primary health care, the recent study uses an explorative hypothesis-generating approach in which the abovementioned discussion is informed by 4 foci of interest and the study aims, as stated in the following section.

#### Focus 1: Ethical, Legal, and Social Issues of SCA Use

We aim to identify the ethical, social, and legal subjects in the recent scientific literature on SCAs (eg, usage linked to inequities in health care, patient autonomy, modification of role concepts and agency).

#### Focus 2: SCA Epidemiology, Users, Nonusers, and Predictors of Use

Our results will contribute to describing the user group and nonuser group of SCAs in more detail. The degree of use of SCAs in Germany will be derived, and predictors for SCA use will be identified. Moreover, vulnerable groups that might be disadvantaged through the implementation of SCAs will be described.

#### Focus 3: Patterns and Impact of SCA Use and the User Level

As a goal for the users’ perspective, a comprehensive description of SCA use will be derived. This will comprise the assessment of requirements that are fulfilled or unfulfilled by SCA use. Additionally, we aim to identify the possible risks associated with SCA use and assess how users handle SCA information and action recommendations. SCA effects on user agency, health and eHealth literacy, well-being, and self-care will also be observed.

#### Focus 4: Impact of SCA Use on Health Care Systems and Health Care Workers

We will specially focus on considering the impact of SCAs from a health system perspective by assessing the following: changes in the patient-physician relationship, strategies of handling preinformed patients, changes in the role concept of physicians and requirements of GP, as well as potential psychosocial risks and demands and perceived work stress resulting from these changes.

## Methods

### Study Design

This study’s areas of focus and corresponding study phases will be conducted by multidisciplinary partners from the areas of social medicine, ethics and medical history, legal studies, general practice, sociology, occupational health medicine, and health services research. We will investigate SCAs that offer self-triage and action recommendations for medical laypersons. The project partners will co-develop study materials, subsequently discuss results, and conduct method workshops throughout the 3 years. During the final study year, a series of workshops will include participants of the preceding study parts. This workshop series during the final year is led by a social scientist with comprehensive experience of working in cross-disciplinary research and holding method workshops. The workshops will also serve as internal quality control and monitoring. An advisory board is continually informed about the progress and the results of the study phases. Members of the advisory board will be recruited from different contexts and disciplines. The advisory board will meet annually to give feedback on the research process, preliminary results, and the dissemination of the latter.

### Ethical Considerations

The German Federal Ministry of Education and Research funds the project for 3 years (Grant 01GP1907A). Ethical approval for this study was obtained from the ethics committee of the University of Tübingen (ID: 464/2020BO). This study will be conducted in accordance with the Declaration of Helsinki. Study participants will be informed thoroughly about the study and their rights, and written informed consent will be obtained from all study participants. Other research ethics requirements such as data protection will be diligently considered. The general study design and the involved research partners are outlined in Figure 1.

**Figure 1 figure1:**
[figure not shown]
Overview of the study design, research partners and analysis methods. IEHM: Institute of Ethics and History of Medicine, University Tübingen, IGP: Institute of General Practice and Interprofessional Care, University Hospital Tübingen, IOSM: Institute of Occupational and Social Medicine and Health Services Research, University Hospital Tübingen, FHWS: University of Applied Sciences Würzburg-Schweinfurt, SCA: Symptom Checker App.

### Study Course

Four main data sources will be considered, each representing a specific stakeholder group of SCAs: representative sample of the German population (divided into SCA user and nonuser), GP, and health care experts. We define SCA users as participants that have used SCAs at least once, and nonusers are participants who never used SCAs. Data collection and analysis methods will comprise qualitative and quantitative approaches.

The different methods are applied to the data sources in 4 interconnected study phases, each representing one of the four main foci of interest of the study: a literature review (study phase 1, lead: Institute of Ethics and History of Medicine, University Tübingen [IEHM], Institute of Applied Social Science, University of Applied Science Würzburg-Schweinfurt), a representative survey of SCA user and SCA nonuser (study phase 2, lead: Institute of General Practice and Interprofessional Care, University Hospital Tübingen [IGP]), an SCA user diary-based self-observation combined with individual semistructured interviews (study phase 3, lead: IEHM), and lastly, single semistructured interviews with GPs and health care experts (study phase 4, lead: Institute of Occupational and Social Medicine and Health Services Research, University Hospital Tübingen [IOSM] for GP interviews, lead: IGP for health care experts interviews). For this study protocol, we will follow the Good Reporting of A Mixed Methods Study (GRAMMS) [27] checklist. Preferred Reporting Items for Systematic reviews and Meta-Analyses extension for Scoping Reviews (PRISMA-ScR) [28,29], STROBE (STrengthening the Reporting of OBservational studies in Epidemiology) [30], SRQR (Standards for Reporting Qualitative Research) [31], and GRAMMS [28] checklists will be applied during the project process. The PRISMA-ScR, STROBE, and SRQR guidelines will be applied on specific study phases. The GRAMMS [28] guideline will be used in the context of mixed methods approaches and in the integration of results. In the following sections, the 4 study phases and their connections are described in detail.

### Study Phase 1: Literature Review

The first study phase will comprise a comprehensive literature review that will assess the existing research on SCAs and their impact on primary care. The aim of this study phase is to gain a clearer picture of the state of science of SCAs, considering the ethical, legal, social, and systemic (eg, risks, potentials) impacts of SCAs. A literature search, oriented on scoping review (ScR) methodology, will be conducted and reported according to the PRISMA-ScR statement [28,29]. In recent years, the ScR methodology has been adopted and further developed for the field of bioethics, which is characterized by normative research questions. When analyzing argumentative literature, adjustments need to be made to the “classic” ScR methodology [32-34]. Key terms will be defined for the search strategy regarding the research questions, and databases covering the relevant dimensions (biomedical, ethical, social, and legal) are selected (Web of Science, PubMed [Medline], Belit/Ethmed, ProQuest, SowiPort, GESIS, Philpapers, Juris, BeckOnline, etc). The inclusion criteria comprise either the mention of an ethical, legal, or social issue or a combination of this terms related to SCAs as a digital or mobile app, targeting medical laypersons that support the assessment of symptoms and self-triage or one of both aspects. Apps for health care professionals or other experts, as well as SCAs, which focus on a single health condition or certain groups of diseases were excluded. To present the full spectrum of ethical, legal, social, and systemic impacts literature relevant to the review question, not only argument-based but also empirical literature was included. Publications on SCAs that were written in English or German and published until 2020 were included in the review. Journal articles, contributions to anthologies, reports, case series, letters to editors, opinions, commentaries, and conference papers were also included; web-based blogs have not been considered. Three researchers screened the identified literature via hand and database search and discarded publications not meeting the inclusion criteria. Publications were analyzed by 2 authors using the method of qualitative content analysis proposed by Kuckartz [35].

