### Study Phase 1: Literature Review

The literature review on ethical, legal, social, and systemic impacts of SCAs was completed in December 2021 and will be published in 2022.

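### The literature review claims four impact domains, but its topic inclusion criterion admits publications on three and leaves out systemic impacts

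*Protocol article*

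**What the plan says.** In Methods, Study Phase 1: Literature Review, the aim is to establish the state of science on SCAs, "considering the ethical, legal, social, and systemic (eg, risks, potentials) impacts of SCAs". The same section gives the topic rule for inclusion: "The inclusion criteria comprise either the mention of an ethical, legal, or social issue or a combination of this terms related to SCAs". It adds that both argument-based and empirical publications were taken in, with the purpose stated as "To present the full spectrum of ethical, legal, social, and systemic impacts literature relevant to the review question". Three researchers screened the records and "discarded publications not meeting the inclusion criteria".

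The four-domain scope appears elsewhere too. The abstract (Methods) says that "a comprehensive literature review will be conducted to assess the ethical, legal, social, and systemic impacts of SCAs". The Results say "The literature review on ethical, legal, social, and systemic impacts of SCAs was completed in December 2021". The Discussion (Principal Findings) lists an overview of literature on the same four kinds of impact first among the expected main findings.

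Two other places give three domains. Focus 1, the objective that the review serves, reads "We aim to identify the ethical, social, and legal subjects in the recent scientific literature on SCAs". Later in Principal Findings, the scoping review is described as one of ethical, social and legal literature.

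**The concern.** A review's eligibility rule should select the literature that its aim names. Here the aim has four limbs and the rule has three. A publication with systemic content and nothing ethical, legal or social has no route into the review, even though its subject is one that the review says it covers.

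What is at stake is how the result is read. The Introduction claims a substantial gap in the literature on the effect of SCAs on health care systems. A review that presents itself as covering systemic impacts, but whose rule does not admit papers on those alone, could find little systemic literature partly because of its own criterion. Readers could then take that as confirmation of the gap. Any such loss would fall on one domain only and would not be visible in the review's output.

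**Working it through.** No arithmetic applies: the point depends on no rate, effect size or sample size, and the plan gives no figure to reproduce. The check is a comparison of wording.

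**Step 1: domains named in each place.**

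| Place in the protocol article | Ethical, legal, social | Systemic |
|---|---|---|
| Abstract, Methods | yes | yes |
| Study Phase 1 (Methods), aim | yes | yes |
| Study Phase 1 (Methods), coverage claim | yes | yes |
| Results, Study Phase 1 | yes | yes |
| Principal Findings, list of main findings | yes | yes |
| Study Phase 1 (Methods), inclusion criterion | yes | **no** |
| Focus 1 | yes | **no** |
| Principal Findings, later description of the scoping review | yes | **no** |

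Five statements name four domains and three name three. The statement that decides what enters the review is among the three.

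**Step 2: does any other eligibility condition bring systemic content in?** The remaining conditions concern the kind of app (aimed at laypersons, supporting symptom assessment or self-triage, not confined to one condition or disease group), language, publication date and publication type. None concerns the topic of the impact. The sentence admitting empirical as well as argument-based literature widens the type of paper and leaves the topic rule as it was.

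**Step 3: apply the rule as written.**

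- A paper on patient autonomy in SCA use mentions an ethical issue and is included.
- An empirical paper on triage load that also remarks on inequities in care is included, because Focus 1 lists inequities among the ethical, social and legal subjects.
- An empirical paper on triage load or avoidable cost with no such remark mentions none of the three, and is discarded.

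Only the third case is affected. The article's Background cites work on risk-averse triage advice and on preventable costs from inaccurate triage, so the kind of literature exists. The documents do not show whether those particular papers also mention an ethical, legal or social issue.

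**Step 4: could *social* already contain *systemic*?** The article lists the two as separate items in every four-domain statement. If one contained the other, the fourth term would be redundant. The boundary is not defined, so it was left to the screeners' judgement.

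**The case against.** The strongest reply is that the coverage sentence shows the authors meant to keep systemic literature, and that the bar is low: one mention of a social issue, with *social* undefined, is enough. Papers on access or on the role of the general practitioner would often pass. This stands as a limit on the size of the problem. It does not remove the mismatch, because intent in one sentence does not alter the rule in another.

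A second reply is that health-system impact has its own objective and data in Focus 4 and Study Phase 4, and that the Discussion expects the competing claims about over- and underuse to be settled by the empirical study of users, not by the review. That is right: the project's systemic conclusions do not rest on the review alone.

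A third is that an article condenses a fuller protocol, which may define screening in more detail. But the point concerns a rule that is stated and that conflicts with the aim stated beside it, not a detail left out.

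A reader might also infer more than the documents support:

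- **That systemic papers were in fact lost, or lost in a known proportion.** The article reports no such loss and gives nothing from which a share could be estimated.
- **That the search missed them too.** The article says "databases covering the relevant dimensions (biomedical, ethical, social, and legal) are selected". The biomedical dimension is included and the list of databases is open-ended, so nothing shows a failure at the search stage. The problem is at screening.
- **That *systemic* has a fixed meaning here.** The aim glosses it only through risks and potentials. Reading it as effects on the health care system fits the Introduction, which speaks of impacts on primary health care systems, but it remains an interpretation.

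**Conclusion.** The inconsistency is real and is not resolved anywhere in the article. The review's aim and claimed coverage include systemic impacts; its topic criterion does not; and Focus 1 and part of the Discussion side with the criterion. Taken literally, the rule excludes publications that address only systemic impacts.

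The number affected is unknown and may be small. The conclusion assumes that screeners applied the criterion as worded and did not stretch *social* to cover system effects. If they did stretch it, fewer papers were lost, but the published criterion then misdescribes the screening. Either way, the article should be corrected before the review's systemic coverage is relied on. The consequence is confined to what the review includes and may conclude.

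**What to change.** Choose one scope and apply it throughout.

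**Option 1: keep the four domains.** Add systemic impacts to the inclusion criterion in Study Phase 1, with a short definition consistent with the aim, and bring Focus 1 and the later Discussion text into line. Have the existing screeners re-check the records discarded for having no ethical, legal or social issue against the added limb. The cost is a small amount of extra screening, provided that exclusion reasons were logged. The article does not say whether they were; if not, more of the discarded records would need a second look. The review is reported as complete, with publication planned for 2022, so this is a supplementary screen.

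**Option 2: keep the criterion.** Limit the review's stated scope and conclusions to ethical, legal and social issues in the abstract, Study Phase 1, the Results and Principal Findings, and say that sparse systemic literature in the review is not evidence of a gap. This costs only wording, but the review gives up its claim to cover systemic impacts.
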